**Methods:**

Prospective, randomized, double blind, non-inferiority, controlled clinical trial

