### Hypothesis

No induction is non-inferior to standard dose induction with basiliximab in low immunological risk kidney transplant recipients.

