### Randomization and blinding

After fulfilling the enrolment criteria and obtaining the informed consent, subjects will be randomized to receive either the standard therapy (Arm I) or placebo (no induction) (Arm II) with a 1:1 allocation, as specified in the intervention section below. A randomization algorithm has been generated by the statistician. The randomization algorithm will be maintained by the Department of Pharmacy and has been generated via the ralloc procedure in Stata™ (Jones and Kenward version 3.7.6), with block randomization: subjects will be divided into subgroups called blocks (block size: 8), such that the variability within blocks is less than the variability between blocks. Then, subjects within each block are randomly assigned to either group. The algorithm will be used to randomize patient following signing the informed consent and admission.

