### Statistical methods

The sample size projection is based upon historical data from transplants in 2018 and for which at least 1 year of follow-up has been achieved. These number 16 subjects and from whom one suffered rejection within the year, i.e., a rate of 0.0625. A margin of non-inferiority is proposed such that the true rejection rate among those treated without Simulect® would not be more than 15%, i.e., a margin of 0.0875 (0.1500 minus 0.0625). We recruit patients for the study and calculate a 95% confidence interval for the true rejection rate among those treated without Simulect®. This confidence interval will be P ± SE(p). We wish that the confidence interval for the rate to be at least 0.0875. The standard error of p is SQRT(p(1-p)/n). Solving for *n* yields a value of approximately 64. Accounting for loss to follow-up and other logistical issues, we have added to this number. We propose that the sample size in each arm be 70 subjects.

Statistical analysis will be performed using SAS/JMP Version 14 (SAS Institute, Cary, NC). Baseline parametric data will be expressed as means of and standard deviations and any differences in the groups will be analyzed with the paired Student’s *t* test, the chi-square test, or the Mann-Whitney *U* test as appropriate. *P* values less than 0.05 will be considered statistically significant. Multivariate analysis will be used to adjust for other risk factors including the concomitant administration of other interacting medications such immunosuppressants. Kaplan-Meier survival analyses will be used to compare outcomes for patient survival, graft survival, rejection, and BK nephropathy. Univariate and multivariable stepwise. Cox regression analyses will be performed to determine risk factors associated with patient death, graft loss, and rejection. We will also use propensity score analyses as an additional means to account for group differences in baseline characteristics. A propensity score represents the likelihood of a patient receiving a particular treatment or, in this case, no basiliximab induction instead of two doses of basiliximab. Data analysis will be carried out after completion of therapy in retrospective manner.

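### The hypothesis compares two randomised arms, but the only non-inferiority procedure described is a one-arm interval set against a 15% ceiling taken from 16 historical patients

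*Protocol article*

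**What the plan says.** The Methods line of the abstract calls the study a "Prospective, randomized, double blind, non-inferiority, controlled clinical trial". The Hypothesis section is comparative: "No induction is non-inferior to standard dose induction with basiliximab in low immunological risk kidney transplant recipients". Under Randomization and blinding, patients go to standard therapy or to "placebo (no induction) (Arm II) with a 1:1 allocation".

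The first paragraph of Statistical methods holds everything said about how non-inferiority will be judged:

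- The reference rate is historical: "These number 16 subjects and from whom one suffered rejection within the year, i.e., a rate of 0.0625".
- The requirement is that "the true rejection rate among those treated without Simulect® would not be more than 15" per cent. The margin of 0.0875 is obtained by subtracting the historical 0.0625 from that 0.15.
- The investigators will recruit patients and "calculate a 95% confidence interval for the true rejection rate among those treated without Simulect".
- The standard error is the square root of p(1-p)/n: one proportion and one n.
- Solving for n gives about 64, raised to 70 per arm for losses and logistics.

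The second paragraph adds Kaplan-Meier comparisons (rejection included), Cox regression for risk factors, multivariate adjustment and propensity scores, with a 0.05 significance level. None of these refers to the margin.

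**The concern.** A non-inferiority claim against basiliximab needs an estimate of how much worse no induction is than basiliximab. An interval for the no-induction rate alone shows only whether that rate is below a fixed number. The number stands in for the control rate plus the margin, so the conclusion depends on one event in 16 past patients instead of on the randomised control group.

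The 15% ceiling and the 0.0875 difference are the same requirement only when the true control rate is 6.25%. If the control rate is lower, the ceiling lets through a difference as large as the margin or larger. If it is higher, the ceiling penalises no induction for a background rate that both arms share. What randomisation and blinding provide, a fair concurrent comparison, is not used for the key inference.

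**Working it through.** **Inputs from the protocol article (Statistical methods):** historical rate 1/16 = 0.0625; ceiling 0.15; margin 0.15 − 0.0625 = 0.0875; 95% interval; SE = √(p(1−p)/n); n about 64, raised to 70 per arm.

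**1. Reproduce the printed 64.** One-sample half-width formula with p = 0.15 and half-width 0.0875:

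n = 1.96² × 0.15 × 0.85 / 0.0875² = 63.97, so 64.

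The same formula with p = 0.0625 gives 29.4. A two-arm non-inferiority calculation at 6.25% in both arms needs 95 or more per arm over the alpha and power values tried (one-sided 0.05 or 0.025; 80% or 90%). The 64 is therefore a one-arm interval calculation with no term for the control arm.

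**2. Turn the one-arm interval into a rule.** Take success as a 95% upper limit below 15%, with n = 70:

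- 5 rejections: 0.0714 + 1.96 × 0.0308 = 0.132, pass.
- 6 rejections: 0.0857 + 1.96 × 0.0335 = 0.151, fail.

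The rule is met with 5 or fewer rejections in the no-induction arm, whatever happens in the basiliximab arm.

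**3. Compare with a two-arm rule.** The comparator is the score (Farrington-Manning) test of the difference, no induction minus basiliximab, against 0.0875 at one-sided 0.025. Probabilities are exact binomial with 70 per arm.

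| True basiliximab rate | True no-induction rate | One-arm rule passes | Two-arm score test passes |
|---|---|---|---|
| 6.25% (protocol) | 15% (protocol) | 3.8% | 2.2% |
| 2% (assumed) | 10.75% (worse by the full margin) | 22.3% | 1.9% |
| 3% (assumed) | 11.75% (worse by the full margin) | 15.5% | 1.9% |
| 4% (assumed) | 12.75% (worse by the full margin) | 10.4% | 2.0% |
| 15% (assumed) | 15% (no difference) | 3.8% | 29.9% |

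In the first four rows the no-induction arm is worse by exactly 0.0875, so a pass is a false claim and should occur about 2.5% of the time. In the last row the arms are equal, so a pass is correct.

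**4. One data set.** With 5/70 rejections on no induction and 0/70 on basiliximab, the one-arm upper limit is 13.2%, under the ceiling. The Newcombe upper limit for the difference is 15.7%, well beyond 8.75 points.

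**5. The anchor.** The exact 95% interval for 1/16 is 0.16% to 30.2%. The control rates assumed in step 3 all lie inside it.

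**6. What the two-arm rule costs.** With 6.25% in both arms and 70 per arm, the score test passes 47% of the time (exact), against 73% for the one-arm rule.

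**The case against.** The strongest objection is that the decision rule is inferred. The interval sentence stands in the paragraph that derives n, and the protocol nowhere writes that non-inferiority is concluded if the upper limit is below 15%. The paragraph could be a precision argument for the sample size, with the primary test left to a statistical analysis plan that is not at hand. That the rule is inferred stands. But the sentence says what will be calculated from the recruited patients, and it is tied directly to the margin. No other non-inferiority criterion appears, and a plan with a two-arm test would conflict with this text. Even as a sample-size argument alone, it sizes a comparative hypothesis on one arm.

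It is also fair that at the protocol's own rates the two rules differ little (3.8% against 2.2%), and that the larger gaps rest on control rates the protocol does not state. The two-arm test fails often too: about 70% of the time at 15% in both arms.

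Four stronger readings are tempting and are not supported:

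- **The basiliximab arm is unused in the analysis.** It enters the Kaplan-Meier comparison of rejection and the propensity-score analyses. It is absent only from the non-inferiority procedure.
- **A non-significant chi-square test would be taken as non-inferiority.** Chi-square is named only for baseline data, and the protocol does not say that a P value above 0.05 shows non-inferiority.
- **The interval is really one standard error wide.** The printed formula lacks its multiplier, but the text says 95% and 64 is obtained with 1.96, so this looks like an omission in print.
- **The plan states two rival criteria.** It states one requirement in two forms, which separate only when the control rate is not 6.25%.

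**Conclusion.** The point holds in this form: the protocol states a comparative hypothesis, but the only non-inferiority procedure it describes, and the sample size built on it, concern the no-induction arm alone. This is a procedure that does not match the hypothesis, so it goes beyond detail left to another document.

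The size depends on the true control rate. At 6.25% the false-claim rate is 3.8% against 2.2% for the score test, a modest excess. At assumed control rates of 2% to 4% with no induction worse by the full margin, it is 22% to 10% against about 2%. At 15% in both arms, the one-arm rule recognises equality 4% of the time against 30%. These figures assume 70 evaluable patients per arm, a Wald interval with 1.96, and the inferred rule that the upper limit must be below 15%. One event in 16 patients does not settle which control rate applies.

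**What to change.** State the primary analysis as the between-arm difference in 12-month biopsy-proven acute rejection, no induction minus basiliximab, with a two-sided 95% score (Miettinen-Nurminen) or Newcombe interval. Claim non-inferiority only if the upper limit is below the stated 0.0875. Report the no-induction rate against 15% as supportive only.

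Replace the one-arm sample-size justification with the power of this comparison: about 47% with 70 per arm and 6.25% in both arms. For orientation, the usual normal-approximation formula, with one-sided 0.025 and 80% power (both assumed, since the protocol states neither for this test), gives (1.96 + 0.8416)² × 2 × 0.0625 × 0.9375 / 0.0875² = 120.1, so 121 per arm.

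The change to the analysis takes one paragraph and needs no new data items. The real cost is that the trial at its present size has less than an even chance of supporting its claim when the arms are equal at 6.25%. The protocol should either say so or revisit the number of patients. The fix does not strengthen the basis of the 0.0875 margin, which still comes from the 1/16 rate.

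### The only numeric criterion set on the confidence interval is reversed: the plan's own n of 64 needs a 95% half-width of at most 0.0875, and the non-inferiority rule should be stated separately

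*Protocol article*

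**What the plan says.** The Hypothesis section states: "No induction is non-inferior to standard dose induction with basiliximab in low immunological risk kidney transplant recipients". Rejection is the primary outcome, so a low rate without induction favours the hypothesis.

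The Statistical methods section of the protocol article opens with the sample-size projection. The historical reference is 2018 transplants: "These number 16 subjects and from whom one suffered rejection within the year, i.e., a rate of 0.0625". The aim is then put as a ceiling on the true rate: "the true rejection rate among those treated without Simulect® would not be more than 15%, i.e., a margin of 0.0875", the 0.0875 being 0.1500 minus 0.0625. The trial will "calculate a 95% confidence interval for the true rejection rate among those treated without" basiliximab, and that interval is printed as the estimate plus or minus one standard error. Next comes the criterion: "We wish that the confidence interval for the rate to be at least 0.0875". The standard-error formula follows, n is solved as about 64, and 70 per arm is proposed to allow for losses.

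The paragraph on analyses that follows lists tests at P < 0.05, Kaplan-Meier, Cox and propensity-score methods. It compares no confidence limit with any bound.

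**The concern.** The criterion asks for something to be large where the design needs it to be small. A precision target caps the half-width of an interval. A non-inferiority claim about an adverse outcome caps an upper limit. "At least" fits neither, and it conflicts with the 15% ceiling given earlier in the same paragraph. The sentence also does not say which feature of the interval it governs: lower limit, upper limit, half-width or full width.

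Non-inferiority is the trial's only hypothesis, and this is the only number attached to the interval. If an analyst took the sentence as the success criterion, a poor result in the no-induction arm would be more likely to satisfy it than a good one. If the analyst set it aside, this document would offer no other stated limit to clear, and the rule could be settled after the data are seen.

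**Working it through.** **Inputs** (Statistical methods, protocol article): reference rate 1/16 = 0.0625; ceiling on the true rate 0.15; margin 0.0875; 95% confidence; SE = √(p(1−p)/n); stated n about 64; 70 per arm.

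**1. Reproduce the stated n.** For a single proportion with half-width w, n = z²p(1−p)/w².

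- z = 1.96, p = 0.15, w = 0.0875: n = 3.8415 × 0.1275 / 0.00765625 = 63.97, i.e. 64. This matches.
- z = 1.96, p = 0.0625, same w: 29.4. No match.
- z = 1, as the interval is printed, p = 0.15: 16.65 with 0.0875 as half-width, 66.6 with 0.0875 as full width. No match.
- The other combinations of p (0.0625, 0.0875, 0.15), z (1, 1.645, 1.96) and half or full width do not match either.

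So the arithmetic used P ± 1.96 SE around 15%, with 0.0875 as the largest acceptable half-width. A larger n shrinks the half-width, so the condition that yields n ≥ 64 is "at most".

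**2. What the sentence does if applied literally to results.** Take n = 70 and the interval x/70 ± 1.96 SE, find the rejection counts x that meet each reading, and sum exact binomial probabilities.

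| Reading | Counts meeting it | True rate 6.25% | 15% | 25% |
|---|---|---|---|---|
| Lower limit ≥ 0.0875 | 13 or more | 0.04% | 24% | 92% |
| Half-width ≥ 0.0875 | 12 to 58 | 0.1% | 36% | 96% |
| Full width ≥ 0.0875 | 3 to 67 | 82% | 99.9% | 100% |
| Upper limit ≥ 0.0875 | 3 or more | 82% | 99.9% | 100% |
| For contrast: upper limit ≤ 0.15 | 5 or fewer | 73% | 3.8% | 0.01% |

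The first four rows rise with the rejection rate over this range. The last row is not a rule in the plan. It is a reviewer's comparison, built from the 15% ceiling, to show what a correctly directed limit does.

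**3. The same with one SE, as printed.** At n = 70 the largest possible SE is √(0.25/70) = 0.060, so a half-width of 0.0875 is never reached at any rejection rate. The lower-limit reading is met with 9 or more rejections, with probability 3% / 74% / 99.6% at the three rates, and so still rises.

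**4. Power of a correctly directed two-arm rule.** The rule is: upper limit of the two-sided 95% interval for the difference (no induction minus basiliximab) below 0.0875. Assume a true rate of 0.0625 in both arms and 70 per arm.

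- SE of the difference = √(2 × 0.0625 × 0.9375 / 70) = 0.0409.
- Normal approximation: Φ(0.0875/0.0409 − 1.96) = Φ(2.139 − 1.960) = Φ(0.179) = 57%.
- Exact enumeration of all pairs of counts with the Wald limit: 62%.

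**The case against.** The strongest reply is that this is a sample-size sentence and not a decision rule. It sits between the margin and the solution for n, begins as a wish, and nothing says that non-inferiority is concluded when it is met. A decision rule may stand in a statistical analysis plan that is not shown. The value 64 also settles the intended meaning, and under that meaning no observed count passes or fails anything. All of this stands, and it limits the point to a misworded planning target plus the need for a separate rule.

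A reader might infer two stronger things. The first is that the margin is being used as a bound on a single rate. The documents do not support this: the bound on the rate is 15%, and 0.0875 entered the calculation as a half-width, which is a distance and a legitimate scale for a difference. The second is that the trial's decision rule rewards excess rejection on every reading. The sentence is not presented as the decision rule, the reading that reproduces n is sound once the inequality is turned round, and with the printed ± SE the half-width reading can never be met at all.

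What the reply does not remove is that the text states the reverse of what its own arithmetic needs. Nor can the sentence, as worded, be taken over as a non-inferiority criterion.

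**Conclusion.** The point holds as a reversed inequality in the only numeric criterion on the interval. The correct planning statement is a 95% half-width, with the 1.96 multiplier, of at most 0.0875 around 15%. That correction leaves both 64 and 70 per arm as they are.

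The consequence lies in the conclusion the trial may draw. As worded, the sentence cannot support the non-inferiority hypothesis, and the section sets no confidence limit against a bound in its place. The probabilities in the table assume 70 evaluable patients, a 95% Wald interval and use of the sentence as a pass/fail test, which the plan does not prescribe. They show why it must not be carried over as the rule; they do not predict what the sponsor will do. The 57 to 62% power rests on an assumed 6.25% in both arms, itself based on one rejection in 16 patients. The document states no power.

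**What to change.** Two changes in the Statistical methods section:

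- Planning sentence: the half-width of the 95% confidence interval (P ± 1.96 SE, at p = 0.15) is to be at most 0.0875. This keeps n at about 64 and 70 per arm.
- Decision rule, stated separately: non-inferiority is concluded if the upper limit of the two-sided 95% confidence interval for the rejection-rate difference, no induction minus basiliximab, is below 0.0875.

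The cost is one or two sentences and no additional patients or data; no increase in enrolment is proposed. The downside is a less favourable stated power: about 57 to 62% for the two-arm rule with 70 per arm and 6.25% assumed in both. That figure should be reported with its assumption, so that failure to show non-inferiority is not misread as evidence of inferiority.

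### The interval formula given for the no-induction rejection rate is a Wald interval; read naturally, its upper limit is too low for about 4 expected events, so false non-inferiority at a true 15% is 3.8% at n = 70 instead of 1.5%

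*Protocol article*

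**What the plan says.** All of this stands in the first paragraph of Statistical methods in the protocol article.

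- The planning rate comes from 2018 transplants: "These number 16 subjects and from whom one suffered rejection within the year, i.e., a rate of 0.0625".
- The ceiling is that "the true rejection rate among those treated without Simulect® would not be more than 15" per cent, from which the margin follows: "i.e., a margin of 0.0875 (0.1500 minus 0.0625".
- After recruitment the team will "calculate a 95% confidence interval for the true rejection rate among those treated without Simulect".
- The form is given as "This confidence interval will be P ± SE(p", and the standard error as "The standard error of p is SQRT(p(1-p)/n".
- Solving for n "yields a value of approximately 64". After an allowance for losses, "We propose that the sample size in each arm be 70 subjects".

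The section names no exact, score or corrected interval. It also does not say which value of p enters the standard error at analysis, or which limit decides non-inferiority. The Hypothesis section states the aim comparatively: no induction is non-inferior to standard basiliximab.

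**The concern.** The formula is the textbook normal-approximation (Wald) standard error. With a rate near 6% and about 70 patients, that approximation is poor. The observed rate drives both the centre and the width of the interval, so the interval narrows when few events are seen, and its upper limit falls too low.

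A non-inferiority claim about the no-induction rate rests on that upper limit. If the limit is too low, the rule passes event counts that a valid 95% interval would reject. The error then runs towards the conclusion that induction can be dropped.

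The sizing also appears to use a different variance. The printed 64 needs the variance at 15%, whereas an interval computed at the observed rate uses a smaller one.

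**Working it through.** **Inputs (Statistical methods).** Planning rate 0.0625; ceiling 0.15; margin 0.0875; n about 64 before the allowance for losses and 70 planned; 95% interval; SE = sqrt(p(1−p)/n).

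**Inferred, not stated.** Multiplier 1.96; p is the observed rate; success means an upper limit below 0.15; the nominal one-sided error is therefore 2.5%.

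**1. Reproduce the plan's n.** n = 1.96² × p(1−p) / 0.0875².
- p = 0.15: 3.8416 × 0.1275 / 0.00765625 = 63.97, which matches the printed 64.
- p = 0.0625: 3.8416 × 0.05859 / 0.00765625 = 29.4, which does not match.

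The sizing therefore used the variance at the ceiling.

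**2. Expected events at 0.0625.** 64 × 0.0625 = 4.0; 70 × 0.0625 = 4.4.

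**3. Upper 95% limits at the counts that matter.** Example for 5 of 70: the rate is 0.0714, SE = sqrt(0.0714 × 0.9286 / 70) = 0.0308, and 0.0714 + 1.96 × 0.0308 = 0.132.

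| Events / n | Wald | Wilson | Clopper-Pearson |
|---|---|---|---|
| 4 / 70 | 0.112 | 0.138 | 0.140 |
| 5 / 70 | 0.132 | 0.157 | 0.159 |
| 6 / 70 | 0.151 | 0.175 | 0.177 |
| 3 / 64 | 0.099 | 0.129 | 0.131 |
| 4 / 64 | 0.122 | 0.150 (0.14997) | 0.152 |
| 5 / 64 | 0.144 | 0.170 | 0.173 |

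**4. Exact binomial error and chance of success.** c is the largest count whose upper limit is below 0.15. False success is P(X ≤ c) at a true rate of 0.15. The chance of success is P(X ≤ c) at a true rate of 0.0625.

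| n | Interval | c | False success at 15% | Success at 0.0625 |
|---|---|---|---|---|
| 70 | Wald | 5 | 3.8% | 73% |
| 70 | Wilson | 4 | 1.5% | 55% |
| 70 | Exact | 4 | 1.5% | 55% |
| 64 | Wald | 5 | 6.8% | 79% |
| 64 | Wilson | 4 | 2.8% | 63% |
| 64 | Exact | 3 | 0.9% | 43% |

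At every n from 60 to 70 the Wald error exceeds 2.5%. It ranges from 3.8% (n = 61 and n = 70) to 8.1% (n = 62). Compared with the exact interval, Wald accepts one more rejection at n = 60, 61 and 66 to 70, and two more at n = 62 to 65.

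**5. Standard error held at the 15% ceiling instead.** The rule becomes x/n + 1.96 × sqrt(0.1275/n) < 0.15. It accepts 4 of 70 (error 1.5%) or 4 of 64 (2.8%), the same as Wilson. The inflation therefore depends on p being the observed rate.

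**6. Between-arm difference.** Assume a control rate of 0.0625, a true no-induction rate of 0.15 and a margin of 0.0875, and sum over both binomial distributions. At n = 70 per arm, false non-inferiority is 3.4% with the Wald difference interval and 2.2% with Newcombe. At n = 64 it is 3.3% and 2.1%.

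**The case against.** The strongest reply is that the formula belongs to the sample-size derivation. It stands directly before the step that solves for n, and the only value of p that reproduces 64 is 0.15. With the standard error held there, the error is 1.5% at n = 70 and 2.8% at n = 64, and there is little to complain about. This stands as a limit on certainty: use of the observed rate is inferred. It does not remove the point, because the text also describes recruiting patients and then calculating the interval. An interval around an estimated rate is most naturally formed with that estimate.

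A reader might infer that the plan sets a rule of an upper limit below 15% at a 2.5% level and breaks it. The article states neither the rule nor the level. They follow from a 95% interval, a 15% ceiling and a non-inferiority hypothesis, and the figures hold only under them.

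A reader might also take 8.1%, or 6.8%, as the trial's error rate. The 8.1% arises only at n = 62, and the 6.8% only if losses bring the analysed number to 64. At the planned 70 it is 3.8%. None of these carries over to the comparative hypothesis, where the Wald excess is about one percentage point (3.4% against 2.5%).

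Part of any departure from 2.5% is binomial discreteness. Wilson itself gives 2.8% at n = 64, where 4 events pass only because the limit is 0.14997.

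Finally, the choice of interval is often left to a statistical analysis plan. Here, however, the article prints a formula, so the point concerns something stated rather than something missing.

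**Conclusion.** The point holds conditionally. If the observed rate enters the printed standard error, the 1.96 multiplier is restored and success means an upper limit below 15%, the Wald interval is too narrow upward. At the planned 70 it accepts 5 rejections instead of 4, and false success at a true 15% is about 1.5 times nominal (3.8% / 2.5%). The excess grows if losses reduce the analysed number to the 64 that the plan calculated before its allowance. For a comparison between arms it is smaller, but in the same direction.

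This ranks below two other problems in the same paragraph: the interval is printed without its multiplier, and it concerns one arm against a fixed ceiling although the hypothesis compares two randomised arms. It remains after the multiplier is restored, and it carries over in reduced form to a Wald interval for the difference.

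**What to change.** Replace the printed interval by a statement along these lines: any single-arm rejection rate is judged on the upper limit of a two-sided 95% Clopper-Pearson interval, and any difference in rejection rates is judged against 0.0875 on the upper limit of a two-sided 95% Newcombe or Miettinen-Nurminen interval. Say explicitly which of these limits decides non-inferiority.

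For the single arm, Wilson is close but can slightly exceed 2.5% (2.8% at n = 64). Only the exact interval guarantees the level.

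The change is one or two sentences, with no extra patients or data. The cost is a stricter rule: at most 4 rejections of 70 instead of 5. The one-arm chance of success at a true 0.0625 and n = 70 is then 55%, not 73%. The sponsor should know that figure before the analysis.

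### The size of 64 (70) per arm is a one-arm precision figure from a misprinted formula; it does not size the two-arm non-inferiority comparison, whose power at 70 per arm is about 47% to 62% under the protocol's own rates

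*Protocol article*

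**What the plan says.** All of the following is in the protocol article, Statistical methods, unless another section is named.

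- The reference rate is historical: "These number 16 subjects and from whom one suffered rejection within the year, i.e., a rate of 0.0625".
- The true rate without basiliximab "would not be more than 15"%, which is expressed as "a margin of 0.0875 (0.1500 minus 0.0625").
- The interval to be calculated is a 95% interval for the rate in the no-induction arm. Its form is given as "This confidence interval will be P ± SE(p"), with the one-sample binomial standard error.
- The precision target reads: "We wish that the confidence interval for the rate to be at least 0.0875".
- Solving for n "yields a value of approximately 64". After an allowance for loss to follow-up, for which no rate is given: "We propose that the sample size in each arm be 70 subjects".

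The Abstract (Methods) calls the trial a randomized, controlled non-inferiority trial. The Hypothesis section states that no induction is non-inferior to basiliximab. Randomization and blinding sets 1:1 allocation. The article states no power and does not say whether the 0.05 significance level is one- or two-sided.

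**The concern.** There are two separate problems.

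First, the paragraph cannot be followed as printed. An estimate plus or minus one standard error is roughly a 68% interval, not 95%. The text does not say which p enters the standard error. A requirement that the interval be *at least* 0.0875 points the wrong way, since a minimum width sets no minimum sample size.

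Second, and more important, the quantity being sized is not the quantity in the hypothesis. The calculation asks how precisely one arm's rate can be estimated. The hypothesis and the margin concern a difference between two randomized arms. That difference carries the variance of both arms and needs a power requirement, and the calculation has neither. Readers will take 70 per arm as adequate for the non-inferiority claim. If it is not, an inconclusive result is quite likely even when the arms are truly equal, and it could be misread as evidence against omitting induction.

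**Working it through.** **Inputs.** Reference rate 1/16 = 0.0625, upper limit 0.15, margin 0.15 − 0.0625 = 0.0875, stated n 64, planned n 70 per arm (all from Statistical methods). Allocation 1:1 (Randomization and blinding). Assumed: one-sided 0.025, matching the 95% interval, and a true rate of 0.0625 in both arms.

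**Step 1: reproduce 64.** For a half-width h and multiplier k, n = k² p(1−p) / h², with h² = 0.0875² = 0.00765625.

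| Multiplier | p = 0.0625, p(1−p) = 0.05859 | p = 0.15, p(1−p) = 0.1275 |
|---|---|---|
| k = 1 (as printed) | 7.65, so 8 | 16.65, so 17 |
| k = 1.96 | 29.4, so 30 | 63.97, so 64 |

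The stated figure is 1.96² × 0.15 × 0.85 / 0.0875² = 63.97. It needs the unprinted 1.96 and p = 0.15, the rate that the margin is meant to exclude. At the expected rate of 0.0625 the same formula gives 30. Reading 0.0875 as the full width does not give 64 either: with k = 1 and p = 0.15 it gives 4 × 16.65 = 66.6.

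**Step 2: loss allowance.** Going from 64 to 70 implies 1 − 64/70 = 8.6% loss, so about 64 evaluable per arm is the planned position after loss.

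**Step 3: two-arm power, normal approximation.** SE of the difference = √(2 × 0.0625 × 0.9375 / n), and power = Φ(0.0875/SE − 1.96).

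- n = 70: SE = 0.0409; Φ(2.14 − 1.96) = 57%.
- n = 64: SE = 0.0428; Φ(2.04 − 1.96) = 53%.

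**Step 4: exact power.** For every pair of rejection counts, weight by the two binomial probabilities and count the pair as a success if the upper 95% limit for the difference is below 0.0875.

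| Rule | 70 evaluable per arm | 64 evaluable per arm |
|---|---|---|
| Newcombe limit, exact enumeration | 47% | 43% |
| Normal approximation | 57% | 53% |
| Wald limit, exact enumeration | 62% | 57% |

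**Step 5: margin detectable with 80% power at 70 per arm.** By normal approximation it is (1.96 + 0.842) × 0.0409 = 0.115. Under the Newcombe rule power at 0.115 is only 72%, and a margin of about 0.125 is needed.

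**Step 6: sensitivity to the reference rate, 70 per arm, equal rates, margin 0.0875.** From a 3% rate to a 15% rate, power runs from 69% to 30% (Newcombe) or from 86% to 30% (normal approximation). This range matters because 0.0625 rests on one event in 16, with an exact 95% interval of 0.2% to 30.2%.

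**The case against.** A reader might infer that 64 is an arithmetic error. It is not: 63.97 follows exactly from 1.96 and p = 0.15. The text names a 95% interval just before the formula, so the missing 1.96 is probably a printing slip, and p = 0.15 gives a larger n than the expected rate would. The fair criticism is that neither is printed. For the same reason nothing shows that a one-standard-error interval will be used in the analysis, so a charge of severe under-coverage in the results would be speculative. The words *at least* did not affect n.

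A reader might also take a single power figure as established. The protocol specifies no two-arm test and no sidedness, so any figure is conditional. With one-sided 0.05 the power at 70 per arm is about 63% to 70%. That is higher, but still below 80%.

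It can also be said that the paragraph describes only a one-arm interval against 15%, and that an analysis plan not shown may define the between-arm test. This is possible, but the size is fixed in the protocol and its basis is stated there. Nor does the one-arm reading rescue it: at a true rate of 6.25% and n = 70, the chance that the upper 95% limit falls below 15% is about 55% (Wilson or Clopper-Pearson) to 73% (Wald).

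What stands is the mismatch between the one-arm calculation and the two-arm hypothesis, together with a formula that does not give the stated result as printed.

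**Conclusion.** The point holds. The only stated basis for the trial's size is a one-sample precision calculation, printed without its multiplier and without the rate used, and with the precision target worded in the wrong direction. It is carried over as the size of each arm in a randomized non-inferiority trial.

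Under the protocol's own rate and margin, with one-sided 0.025 assumed, none of the three two-arm rules reaches 80% power at 70 evaluable per arm, and all are lower at 64. The shortfall depends on the true rejection rate. At rates well below 6.25% a liberal method can exceed 80% (86% at a 3% rate by normal approximation), while at 15% power is about 30%. The documents do not support a flat statement that the trial is a coin toss, nor a claim that the sample size was miscalculated as a precision figure.

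**What to change.** Restate the sample-size paragraph; enrolment is unchanged.

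1. Print the interval as P ± 1.96 × SE(p), state that p = 0.15 was used, replace the *at least* wording with a half-width of at most 0.0875, and describe 64 as a one-sample precision figure.
2. State that the non-inferiority conclusion rests on the 95% confidence interval for the between-arm difference (no induction minus basiliximab) against the 0.0875 margin, with the one-arm interval as descriptive. If an analysis plan already defines the test, the two texts should agree.
3. State the two-arm power at 70 and 64 evaluable per arm, with its assumptions and one named method throughout, because the methods differ enough that mixing them would contradict itself:
   - Newcombe: 47% and 43%; 69% to 30% over control rates of 3% to 15% at 70 per arm; margin for 80% power about 0.125.
   - Normal approximation: 57% and 53%; 86% to 30%; margin for 80% power about 0.115.
4. Note that 6.25% rests on one event in 16 (exact 95% interval 0.2% to 30.2%).

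The cost is a text correction. The downside is that the stated precision and power become less favourable, and disclosure alone does not raise the power.
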